### Sediment

As mentioned before, urinary sediment investigation will be performed under protocollized circumstances at the Laboratory for Clinical Chemistry. It could be argued that this should be done in the GP surgery, as this is more in accordance with common practice. However, if urinary sediment proves to be useful under the optimal conditions of the laboratory, it will be repeated under daily practice conditions in a sub-study after the main study has been completed. The originally obtained sediment data can then be replaced in our model by the daily practice results, using Deming (orthogonal) regression analysis. [70-76] Briefly, this is a method that can be used to estimate the relationship between two measurements with proportional errors, in this case sediment under optimal conditions and sediment under daily practice conditions. The data collection of this sediment sub-study will take place during a specially organized training session, where sediment scoring results of GPs and/or GP assistants will be measured before and after training by experts. Sediment investigation on the same samples will be performed by experts under optimal conditions (= reference standard). The before-training measurements as well as the after-training measurements will be compared with the expert measurements using Deming regression.

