### Clinical assessments (see table 1)

**Table 1 T1:** Assessment schedule

	**GP or GP assistant**	**Patient**
**day 1 (baseline)**	Check availability	
	Obtain informed consent	
		Collect urine at GP surgery
	Perform dipstick and dipslide (and optionally sediment)	Fill in questionnaire
	Send urine to laboratory (refrigerated) for culture and sediment	

**day 2**	Examine dipslide	

**day 1 till day 7**		Record symptoms in diary

**day 8**	If patient did not use antibiotic: collect urine and send for culture	

After eligibility has been confirmed and informed consent has been obtained, urine is collected in a sterile container. Instructions for the collection method may be given at the GP's discretion, but are not necessary, as they have been reported to have no consequences for the extent of contamination. [50-52] We insist that the urine sample is collected at the GP surgery, since collection at home will cause at least some specimens to remain non-refrigerated for too long, thus rendering urinalysis unreliable.[53]

After urine collection, patients are asked to fill in a detailed questionnaire to record presence and severity of signs and symptoms (see additional file 1). Furthermore, they are given a special diary, in which they are to record clinical symptoms and any use of antibiotics for 7 days.

The GP or GP assistant performs a dipstick test (Multistix^® ^5, Siemens Medical Solutions Diagnostics™) and a dipslide test (Uricult^® ^classic, Orion diagnostica™). Dipsticks will be assessed automatically by a Clinitek Status^® ^analyzer (Siemens Medical Solutions Diagnostics™) to reduce inter-observer variation.

Immediately after dipstick and dipslide investigations have been performed, urine samples are stored in a refrigerator at the GP surgery. Within 8 hours they are transported to two laboratories (see below) at 4°C by a specialized courier service.

GPs are free to perform a urinary sediment investigation, the results of which will then be documented. However, in the statistical analysis we will assess the diagnostic value of the urinary sediment investigation performed by experts at the Laboratory for Clinical Chemistry of the Academic Medical Center in Amsterdam. Only if the sediment investigation proves to be useful under the optimal conditions of the laboratory, we will repeat it under daily practice conditions in a sub-study to be carried out after the main study has been completed (see further).

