#### Variable selection

At the time of writing, a failsafe model selection strategy on which all statisticians and other experts in diagnostic and predictive modeling agree does not appear to exist. However, in his book 'Regression modeling strategies (2001)'[62], Harrell made some general proposals for researchers to tailor to the specific circumstances. We intend to use penalized logistic regression, and Tibshirani's *lasso *(least absolute shrinkage and selection operator)[63] in particular to combine the requirements of counteracting over-optimism (shrinkage of regression coefficients) while leaving the opportunity that some coefficients are set to zero, which serves the requirement of a parsimonious model. Bootstrapping will be used to estimate the penalization coefficient.[62] As a form of sensitivity analysis, we shall also explore bootstrapped stepwise regression[64,65] to see how well these approaches concur. We will avoid univariable preselection of predictors. The linearity assumption will be checked for all continuous predictors.

Discrimination of the model(s) will be visualized in high resolution histograms and summarized as 5^th^, 10^th^, 25^th ^50^th^, 75^th^, 90^th^, and 95^th ^centiles of these, Brier score and the area under the receiver operating characteristics curve (ROC) with 95% confidence intervals (overall discrimination).[66]

Using the regression coefficients of the independent diagnostic indicators, an easy to use, multivariable diagnostic rule (clinical index) will be derived, consisting of relevant tests and their diagnostic values.

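### Converting laboratory sediment values through a Deming line leaves random GP misreading out of the substituted model, so that model cannot show what daily-practice sediment loses

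*Protocol article*

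**What the plan says.** All references are to the protocol article.

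- **Main analysis.** Under Clinical assessments, the sediment variable is the laboratory reading: "in the statistical analysis we will assess the diagnostic value of the urinary sediment investigation performed by experts". GP sediment in the cohort is optional: "GPs are free to perform a urinary sediment investigation, the results of which will then be documented".
- **Sub-study.** Only if laboratory sediment proves useful is sediment repeated under daily practice conditions, "in a sub-study after the main study has been completed" (Sediment). On the source of those readings: "The data collection of this sediment sub-study will take place during a specially organized training session". Experts read the same session samples, and GP or assistant readings from before and after training are each compared with the expert readings by Deming regression.
- **Substitution.** "The originally obtained sediment data can then be replaced in our model by the daily practice results, using Deming (orthogonal) regression analysis". Of Deming regression the text says that "this is a method that can be used to estimate the relationship between two measurements with proportional errors".
- **Model and measures.** Under Variable selection: "We intend to use penalized logistic regression", the lasso in particular. Performance is summarised by centiles of the predicted probabilities, the Brier score and the ROC area.

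The text states no step that adds scatter around the line, corrects a coefficient for measurement error, or fits the model to actual GP readings.

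**The concern.** The Sediment section concedes that reading in the GP surgery is closer to usual practice and answers this with the sub-study and the substitution. The question is whether sediment keeps its added value when GPs or their assistants read it. Their readings can differ from the expert's in two ways: systematically (offset and scale) and randomly (scatter). A fitted line carries only the systematic part, while loss of discrimination comes from the random part. A model using line-converted values would therefore give daily-practice sediment the diagnostic value of laboratory sediment.

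The protocol also plans to use threshold probabilities to judge which tests are superfluous (Variable selection strategy, General objectives). A rule that overstates what a GP's sediment reading contributes would produce probabilities that are too extreme for that purpose.

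**Working it through.** The documents attach no figure to this substitution, so there is nothing to reproduce.

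**1. What the substitution does (algebra, no assumed inputs).** Let X be the expert value and R = a + bX, with b > 0, the converted value. A refitted logistic model in R is

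logit p = c0 + c1·R + other terms = (c0 + c1·a) + (c1·b)·X + other terms.

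This is the model in X with a shifted intercept and a rescaled coefficient. Fitted probabilities, their centiles, the Brier score and the AUC are identical. A lasso on standardised predictors also gives the same fit, because R and X standardise to the same variable; without standardisation only the amount of shrinkage changes. The before-training and after-training lines have different a and b but lead to the same fitted model.

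**2. When the conditions fail.**
- *Coefficients kept:* the weight of sediment relative to the other predictors changes by the factor b, so probabilities, Brier score and multivariable AUC can move.
- *Fixed cut-off on the GP scale:* the conversion moves the equivalent cut-off on the expert scale, so sensitivity and specificity shift.
- In both cases each woman's converted value is still an exact function of her expert value, so random misreading does not enter.

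**3. Size for sediment alone (all inputs assumed).** Prevalence 50%; expert value normal with SD 1 in each group and means 1.2 apart.
- Expert AUC = Φ(1.2/√2) = 0.802. The converted value gives the same.
- Overall variance of the expert value = 1 + 1.2² × 0.25 = 1.36.
- If the expert reading explains a share r of GP-reading variance, the added error variance on the expert scale is v = 1.36 × (1 − r)/r, and the GP-reading AUC is Φ(1.2/√(2(1 + v))).

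| r | v | GP-reading AUC | Hidden loss |
|---|---|---|---|
| 0.8 | 0.340 | 0.768 | 0.034 |
| 0.6 | 0.907 | 0.731 | 0.071 |
| 0.4 | 2.040 | 0.687 | 0.115 |

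**4. Size in a model with one other predictor (simulation, inputs assumed).** 40,000 women and a 200-sample session; true sediment SD 1; expert error SD 0.2; GP reading = 0.3 + 0.8 × true value + error; log-odds 1.2 per SD of sediment and 0.5 per unit of a correlated covariate. The expert reading explains 0.64/(1.04 × (0.64 + s²)) of GP-reading variance, where s is the GP error SD.

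| | s = 0.5 | s = 1.0 | s = 1.5 |
|---|---|---|---|
| Variance explained | 0.69 | 0.38 | 0.21 |
| Model AUC, expert | 0.8134 | 0.8104 | 0.8131 |
| Model AUC, Deming-converted | 0.8134 | 0.8104 | 0.8131 |
| Model AUC, actual GP readings | 0.7883 | 0.7554 | 0.7412 |
| Hidden loss in model AUC | 0.025 | 0.055 | 0.072 |
| Brier, expert and converted | 0.1763 | 0.1777 | 0.1765 |
| Brier, actual GP readings | 0.1875 | 0.2006 | 0.2059 |

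At s = 1.0, sediment alone falls from 0.789 to 0.684 (loss 0.105), against 0.055 in the model, so the other predictor absorbs about half.

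**5. Using the converted rule on real GP readings (same simulation).** AUC 0.783, 0.722 and 0.676; calibration slope 0.75, 0.41 and 0.24. Slopes below 1 mean that predictions are too extreme.

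**6. Does adding residual error help?** Adding scatter estimated from the session to the converted values gives model AUC 0.787, 0.748 and 0.737, close to the 0.788, 0.755 and 0.741 from actual GP readings.

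**The case against.** The strongest case against has five parts.

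- **The mechanism is inferred.** The article does not literally say that bare fitted-line values are used, and a condensed article can leave detail to a fuller plan. This stands as a caution. But the session readings do not belong to cohort women, the article names one method for one purpose, and conversion through the line is the only route it gives. If the full plan adds residual scatter, the point falls away.
- **The invariance has conditions.** It needs a linear term and a refit, and the article does not state the refit. This stands, and the claim is limited accordingly. The alternatives still leave random misreading out.
- **A reader might infer that the sub-study as a whole hides GP error, giving the same answer whatever the quality of the readings.** The documents do not support that. Both sets of GP readings are compared with expert readings on the same samples, and that comparison can show bias and scatter. Only the substituted model is blind to them.
- **A reader might also infer that Deming regression is misdescribed.** That is not established. Proportional errors can mean error variances in a constant ratio, the usual Deming assumption, and the word orthogonal in brackets need not fix that ratio at one.
- **The sizes rest on assumed inputs, and the step is conditional, later and optional in wording.** Both are true. They limit the size and priority of the point but do not make the substitution work.

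**Conclusion.** The point holds in limited form. As stated, the substitution cannot show the loss of diagnostic value caused by random GP reading error. With a refitted model and a linear sediment term this is exact: probabilities, AUC and Brier score equal those from laboratory sediment. With kept coefficients or a cut-off the figures may change, but not because of misreading.

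The size is not known from the documents. Under the assumptions shown, the hidden loss for sediment alone is about 0.03 to 0.12 in AUC when the expert reading explains 80% to 40% of GP-reading variance. In the two-predictor simulation it is 0.025 to 0.072, over an explained share of 69% down to 21%.

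This is an analysis choice that cannot serve its stated purpose, not a detail left to another document. It should be changed before the sub-study is analysed. It does not touch the primary objective, the telephone model or the estimates for laboratory sediment.

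**What to change.** Replace the substitution step in the Sediment section with the following:

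1. From the paired session readings, estimate the distribution of the GP or assistant reading given the expert reading: a regression with its residual variance, or a cross-classification if results are graded. Do this separately before and after training.
2. For each cohort woman, draw GP readings from that distribution as in multiple imputation, so that uncertainty in the session estimates is carried through. State the assumption that, given the expert reading, GP error does not depend on the culture result.
3. Refit the diagnostic model on the drawn readings and report AUC, Brier score and the sediment coefficient beside those for laboratory sediment.
4. Keep Deming regression to describe systematic bias between GP and expert.
5. Use the optional GP sediments documented at baseline only as a rough check, since they come from a self-selected subset.

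The cost is a change of wording and some programming; the paired readings are already planned and no new data are needed. The reported value of daily-practice sediment will probably be lower and its interval wider.

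### If the sediment substudy's Deming regression is fitted as orthogonal regression, the comparison of GP readings before and after training can mix random with systematic error

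*Protocol article*

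**What the plan says.** The Sediment section under Substudies plans to carry the laboratory sediment results over to daily practice: "The originally obtained sediment data can then be replaced in our model by the daily practice results, using Deming (orthogonal) regression analysis". It then explains Deming regression: "this is a method that can be used to estimate the relationship between two measurements with proportional errors".

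At a training session, GPs or their assistants score samples before and after being trained by experts. The comparator is described so: "Sediment investigation on the same samples will be performed by experts under optimal conditions (= reference standard". Two fits follow: "The before-training measurements as well as the after-training measurements will be compared with the expert measurements using Deming regression".

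The substudy is conditional, as Clinical assessments states: "Only if the sediment investigation proves to be useful under the optimal conditions of the laboratory, we will repeat it under daily practice conditions".

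The article gives no error variances, no error ratio, no number of samples and no number of readings per sample for this substudy.

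**The concern.** Deming regression allows for error in both measurements but needs the ratio of their error variances. Orthogonal regression is the special case in which that ratio is 1. The section uses the two names as equivalents, while contrasting experts under optimal conditions with GP or assistant readings that are to be improved by training. That contrast gives reason to expect larger random error in the GP readings. The phrase about proportional errors can mean a constant ratio of error variances or errors that grow with the level, and neither meaning implies equal errors.

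The planned pair of fits makes this matter. If training reduces GP random error, the ratio differs between the two stages, so no single fixed value suits both. With the ratio held at 1, less random error in the GP readings lowers their variance, while the expert variance and the covariance stay as they were. The fitted slope must then move, and an analyst could read the movement as a change in systematic over- or under-reading. At stake is the conclusion about what training changed.

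**Working it through.** **Inputs.** The article states no figure to reproduce. All variances below are assumptions: between-sample variance of the true value 1; expert error variance *e* = 0.02, 0.05, 0.10 or 0.20; GP error variance *k·e*, with *k* = 1, 2, 4 or 9; errors independent; expert reading on the x-axis, GP reading on the y-axis.

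**Formula.** For a ratio L of GP to expert error variance, the Deming slope is

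b = [Syy − L·Sxx + √((Syy − L·Sxx)² + 4·L·Sxy²)] / (2·Sxy).

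With true slope 1: Sxx = 1 + e, Syy = 1 + k·e, Sxy = 1. Setting L = 1 (orthogonal) gives b = [d + √(d² + 4)]/2, where d = (k − 1)·e.

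**Example.** With e = 0.10 and k = 4, d = 0.30 and b = (0.30 + √4.09)/2 = 1.161. With k = 9, d = 0.80 and b = (0.80 + √4.64)/2 = 1.477.

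**Orthogonal slope when the true slope is 1:**

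| Expert error variance | k = 1 | k = 2 | k = 4 | k = 9 |
|---|---|---|---|---|
| 0.02 | 1.000 | 1.010 | 1.030 | 1.083 |
| 0.05 | 1.000 | 1.025 | 1.078 | 1.220 |
| 0.10 | 1.000 | 1.051 | 1.161 | 1.477 |
| 0.20 | 1.000 | 1.105 | 1.344 | 2.081 |

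With L set to the true *k*, the slope is 1.000 in every cell.

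**Before and after training, e = 0.10, systematic relation unchanged:**

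- True slope 1, ratio falling from 4 to 2: the orthogonal slope moves from 1.161 to 1.051.
- True slope 1, ratio falling from 4 to 1: from 1.161 to 1.000, an apparent correction of a bias that was not there.
- True slope 1, ratio staying at 4: 1.161 both times, so nothing appears to change.
- True slope 0.8, ratio falling from 4 to 1: at k = 4, Syy = 0.64 + 0.40 = 1.04, Sxx = 1.10, Sxy = 0.80, so b = (−0.06 + √2.5636)/1.6 = 0.963. At k = 1, b = 0.800. Training would appear to create a bias.

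**Errors growing with the level.** A simulation with constant coefficients of variation (lognormal true values, 1000 runs, 1000 samples, true slope 1) gave mean orthogonal slopes of 1.000, 1.049, 1.143 and 1.216 for expert/GP coefficients of 10%/10%, 10%/20%, 10%/30% and 20%/40%. With the true ratio, and over sample sizes of 50, 100 and 1000, the mean was 0.998 to 1.006, except 1.024 at 50 samples with 20%/40%. At 50 samples the orthogonal bias is smaller than the sampling standard deviation of a single slope (10%/30%: mean 1.148, standard deviation 0.189).

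**The case against.** The strongest reply is that the point hangs on one bracketed word. The section nowhere says that the errors are equal or that the ratio is fixed at 1. Its description of proportional errors and its last sentence, which says only Deming regression, both fit general Deming regression, and orthogonal may be a loose synonym. Larger GP error is an inference. The ratio and the number of readings are details that a journal article may leave to the full plan. All of this stands, and it makes the point conditional. It does not remove the conflict between the named method and the described comparison, and general Deming regression would still need a ratio suited to each stage.

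Three stronger readings are tempting and are not supported:

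- *That training will seem to correct a non-existent bias.* This needs a ratio fixed at 1, a true slope near 1 and a fall in GP random error. The article states none of these, and with a true slope of 0.8 the appearance reverses.
- *That the design has one reading per reader and sample, so the ratio cannot be estimated.* The article gives no number of readings.
- *That too steep a slope makes the sediment weight per unit of GP reading too small in the diagnostic rule.* A noisier reading deserves a smaller weight. If errors are independent of culture status, the best GP weight relative to the expert weight is about (1 + e)/(1 + k·e). At e = 0.10 this is 1.10/1.40 = 0.79 for k = 4 and 1.10/1.90 = 0.58 for k = 9. The orthogonal conversion gives 1/1.161 = 0.86 and 1/1.477 = 0.68, and the corrected slope gives 1.00. The orthogonal weight is thus too large, if anything, and correcting the ratio moves it further off. Simulated single-predictor logistic models (log-odds slopes 0.5, 1 and 2; e = 0.05, 0.10 and 0.20; k = 4 and 9) gave the same ordering in all 18 scenarios.

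**Conclusion.** The point holds in a limited form. The section equates Deming with orthogonal regression while comparing readings that it presents as differing in quality, at two stages between which their error may change. If the named method is followed literally, and GP random error exceeds expert error and falls with training, the two fitted slopes differ without any change in the systematic relation.

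The size depends on quantities that the article does not give. The bias is nil at a ratio of 1. It is 1-3% at ratios of 2 to 4 if expert error variance is only 2% of between-sample variance. It reaches 34% at ratio 4, and 108% at ratio 9, if that share is 20%. The direction of the apparent training effect depends on the true slope.

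The consequence is a possible misreading of the before/after comparison in a later substudy that runs only if laboratory sediment proves useful. The primary objective and the main diagnostic models on laboratory sediment are unaffected.

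**What to change.** 1. Delete the bracketed word orthogonal, unless equal error is intended and can be justified.
2. Use a separate error ratio before and after training. If the same readers score a subset of samples twice in the planned session, masked to their first score, estimate the expert and GP error variances from these repeats. If no repeats are made, report each slope over a stated range of ratios, for example 1 to 9.
3. Report random error and systematic bias separately at each stage, so that a gain in precision is not read as removal of bias.
4. Do not present the corrected Deming slope alone as improving the weight of GP sediment readings in the diagnostic rule.

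The cost is wording plus either a slightly longer training session or a wider reported range for the slope. The substudy follows the main study, so nothing already collected is affected.

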### Chlamydia/gonorrhoea

Apart from a UTI, dysuria and urinary frequency in sexually active women may be a result of a urethritis caused by *Chlamydia trachomatis *or *Neisseria gonorrhoeae*. Therefore a polymerase chain reaction (PCR) for *Chlamydia trachomatis *and *Neisseria gonorrhoeae *will be done in each urine sample. An attempt will be made to extend our diagnostic rule for *Chlamydia trachomatis *and *Neisseria gonorrhoeae *infections in women with painful and/or frequent micturition. To attain this, we will perform a polytomous logistic regression analysis, a technique that is used to simultaneously estimate probabilities of multiple diagnoses. [77-79] As a result, a diagnostic model with three outcomes (UTI, *Chlamydia trachomatis*, and *Neisseria gonorrhoeae*) can be derived.

